# The Building Emotional Awareness and Mental health (BEAM) program developed with a community partner for mothers of infants: protocol for a feasibility randomized controlled trial

**DOI:** 10.1186/s40814-023-01260-y

**Published:** 2023-03-09

**Keywords:** Parenting, Maternal, Mental health, Feasibility, Pilot, Randomized controlled trial, mHealth

## Abstract

**Background:**

Drastic increases in the rates of maternal depression and anxiety have been reported since the COVID-19 pandemic began. Most programs aim to improve maternal mental health or parenting skills separately, despite it being more effective to target both concurrently. The Building Emotional Awareness and Mental health (BEAM) program was developed to address this gap. BEAM is a mobile health program aiming to mitigate the impacts of pandemic stress on family well-being. Since many family agencies lack infrastructure and personnel to adequately treat maternal mental health concerns, a partnership will occur with Family Dynamics (a local family agency) to address this unmet need. The study’s objective is to examine the feasibility of the BEAM program when delivered with a community partner to inform a larger randomized controlled trial (RCT).

**Methods:**

A pilot RCT will be conducted with mothers who have depression and/or anxiety with a child 6–18 months old living in Manitoba, Canada. Mothers will be randomized to the 10 weeks of the BEAM program or a standard of care (i.e., MoodMission). Back-end App data (collected via Google Analytics and Firebase) will be used to examine feasibility, engagement, and accessibility of the BEAM program; cost-effectiveness will also be examined. Implementation elements (e.g., maternal depression [Patient Health Questionnaire-9] and anxiety [Generalized Anxiety Disorder-7]) will be piloted to estimate the effect size and variance for future sample size calculations.

**Discussion:**

In partnership with a local family agency, BEAM holds the potential to promote maternal-child health via a cost-effective and an easily accessible program designed to scale. Results will provide insight into the feasibility of the BEAM program and will inform future RCTs.

**Trial registration {2a}:**

This trial was retrospectively registered with ClinicalTrial.gov (NCT05398107) on May 31st, 2022.

**Supplementary Information:**

The online version contains supplementary material available at 10.1186/s40814-023-01260-y.

## Administrative information

Note: The numbers in curly brackets in this protocol refer to SPIRIT checklist item numbers. The order of the items has been modified to group similar items

### Trial Registration – Data Set {2b}

**Table Taba:** 

**Primary registry and trial identifying number**	ClinicalTrials.gov, NCT05398107
**Date of registration in primary registry**	31 May, 2022
**Primary Sponsor**	University of Manitoba
**Contact for public queries**	[name] [[contact]]
**Contact for scientific queries**	[name] University of Manitoba, Winnipeg, Manitoba, Canada
**Public title**	A Community Partnership with Family Dynamics to Examine the Building Emotional Awareness and Mental health (BEAM) Program for Mothers of Young Children
**Scientific titles**	The Building Emotional Awareness and Mental health (BEAM) Program Developed with a Community Partner for Mothers of Infants: Protocol for a Feasibility Randomized Controlled Trial
**Countries of recruitment**	Canada
**Health condition(s) or problem(s) studied**	Depression, Anxiety
**Interventions**	*Intervention*: Building Emotional Awareness and Mental health (BEAM) program
	*Comparator*: MoodMission
**Key inclusion and exclusion criteria**	*Age of eligibility for study:* ≥ 18 years old *Inclusion Criteria:* Identifies as a mother; Has a child 6–18 months old; Resides in Manitoba, Canada; has access to a cellular network; > 9 on the Patient Health Questionnaire-9 and/or Generalized Anxiety Disorder-7; Meets criteria for a major depressive disorder and/or anxiety disorder on the Mini International Neuropsychiatric Interview (MINI); Completed the pre-intervention survey before randomization; Available to attend weekly telehealth sessions; Comfortable with English (spoken and written) *Exclusion Criteria*: Suicide attempt in the past year; Self-harm in the past 6 months; Clinically significant psychotic symptoms, posttraumatic stress disorder, or severe alcohol use disorder on the MINI which would interfere with the mother’s ability to attend and/or benefit from services.
**Study type**	Intervention
	*Allocation:* Randomized *Intervention Model*: Parallel Assignment *Masking*: Unblinded
	*Primary purpose*: Treatment
	Pilot and Feasibility
**Date of first enrolment**	February 2022
**Target Sample Size**	80
**Recruitment status**	Active, not recruiting
**Primary Outcomes**	1. Recruitment Rate 2. Retention Rate 3. Perceived Usefulness 4. Processing Time 5. Post-Intervention Questionnaire Completion Time 6. Follow-Up Questionnaire Time 7. Questionnaire Completion 8. Treatment Adherence 9. Safety
**Secondary Outcomes**	1. Treatment Response 2. Treatment Effect 3. Baseline Severity Moderation
**Demographic Variables**	1. Sociodemographics 2. Adverse Childhood Experiences 3. Program Feasibility and Acceptability

### Protocol Version {3}

February 2023, Version 2

### Role of Sponsor {5c}

The funding source had no role in the design of this study and will not have any role during its execution, analysis, interpretation of data, or decision to submit results for publication.

### Committee roles and responsibilities {5d}

*Principle Investigators and Co-Investigators:* Study planning; Organization of Parent Advisory Board (PAB); Design and conduct of trial; Preparation of protocol and revisions; Application to ethics review board; Recruitment; BEAM Administration; Reporting of adverse events; Responsible for master file; Budget administration; Data verification; Conduct and interpret analyses; Publication of study reports

*Community Partner, Family Dynamics*: Design of study; Recruitment; BEAM Administration; Interpretation of findings

*Parent Advisory Board (PAB):* Design of trial; BEAM Administration; Interpretation of findings

## Introduction

### Background and rationale {6a–b}

Maternal depression and anxiety have dramatically increased during the COVID-19 pandemic [1]. A meta-analysis documented that 26.9 and 41.9% of mothers experience clinically significant depression and anxiety symptoms, respectively [2]. Key risk factors associated with increased maternal mental health concerns include stressors associated with isolation, domestic conflict, and a lack of parenting support [1, 3]. The absence of standard mental health screening and a backlog of existing mental health services suggests most mothers do not have access to evidence-based mental health treatments [4, 5]. In Canada, only 1 in 10 mothers receive adequate postpartum mental health care, resulting in persistence of problems, enormous individual and societal economic impact, as well as child mental health concerns and developmental impairments [6–9]. The national WeCanForKids report highlighted a need to address maternal mental health even prior to the COVID-19 pandemic [10]. With significant elevations in maternal depression and anxiety compared to pre-pandemic rates [1], there is now a critical need to mitigate the impact of maternal mental health concerns among at-risk families to reduce negative sequelae.

Existing therapies are insufficient to address family mental health needs. Programs designed to improve parent mental health and parenting skills separately have small effects with minimal improvements in the past 20 years [11]. Although programs addressing both mother and child mental health have 50% larger effects than treating either alone, these programs are typically costly, require extensively trained clinicians, and have lengthy waitlists, in turn impeding program scalability and ability to meet maternal mental health needs [12]. Early models of mobile health (mHealth) programs show promise for treating depression and anxiety but are rarely targeted toward mothers and have high dropout rates [13, 14]. Further, mHealth is typically delivered by a third party, without consulting trusted community agencies who hold key knowledge of local needs, can appraise risk, and offer additional support if required.

The Building Emotional Awareness and Mental health (BEAM) program is a mHealth program designed to mitigate the impacts of stress on family mental health and the program’s feasibility is ready to be tested in partnership with an established community agency. The BEAM program was co-designed with a patient advisory board (PAB, i.e., mothers with lived experience managing depression and/or who have completed a previous trial [15]) based on identified priorities of connecting therapists and mothers in a secure online setting. The BEAM platform enables the merger of telehealth best practices with peer connection. Key elements of the BEAM program include the following: (a) expert-led psychoeducational videos adapted from the Unified Protocol (UP), an evidence-based cognitive-behavioral therapy for depression, anxiety, and associated disorders [16–18], as well as emotion-focused parenting strategies [15]; (b) structured telehealth (videoconferencing) group sessions to consolidate therapeutic content and build social support [19, 20]; (c) a monitored online forum to enhance peer connection; (d) symptom monitoring to track progress [21]; and (e) suggested assignments such as reflections and practice exercises. BEAM is therapist-led to increase adherence, consistent with evidence that guided mHealth therapy is more effective than unguided [22]. The BEAM program holds strong potential as a scalable model that can be readily adapted to meet maternal needs, specifically among underserved populations.

Family agencies typically lack the infrastructure and personnel capacities to adequately treat maternal mental health concerns [23], with this gap in services being stark in Manitoba, Canada, where mothers wait 12–18 months for therapy on provincial public health waitlists. At our partner agency, Family Dynamics, parenting coaches find untreated maternal depression and anxiety to be primary in-home risk factors that impede the efficacy of parenting interventions. Providing BEAM training and consultation will enable coaches to provide expert-led mental health treatment to supplement and expand upon existing services. Our partnership approach with Family Dynamics will allow for the assessment of the BEAM program's feasibility when delivered with a community partner.

Our pilot, non-superiority trial of the BEAM program among mothers of toddlers (*N* = 65) found clinically significant change in 66.7% of mothers with persistent depression (anxiety symptoms were not assessed) [24]. Qualitative feedback suggests high acceptability (e.g., “[BEAM] was so helpful in establishing how to accomplish my goal. I also enjoyed getting to know the group via zoom and feel much more comfortable chatting in the forum”; “[BEAM] made me feel less alone in the issues I am facing personally, mental health wise, and in parenting”). This trial was not conducted with mothers of infants and did not include a partnership with an established community agency, however. To inform scalability efforts, further research is needed to determine the feasibility of the BEAM program when delivered in collaboration with a community agency. Following the Obesity-Related Behavioral Intervention Trials (ORBIT) model for developing behavioral treatments for chronic disease [25, 26], our team will complete a feasibility randomized controlled trial (RCT) of the BEAM program. Implementation elements (e.g., maternal depression and anxiety) will be examined to estimate effect size and variance for future sample size calculations and will be compared to a Standard of Care (SOC), i.e., MoodMission. MoodMission was chosen as the SOC as this program has been rigorously studied using RCTs, which is rare for a mHealth app and shows a decrease in moderate depressive and anxiety symptoms post-intervention [27–30].

### Objectives {7}

#### Aim 1

To examine the feasibility of the BEAM program when delivered by a community agency. Feasibility indicators include recruitment rate, retention rate, and perceived usefulness of BEAM, for example.

#### Aim 2

To assess preliminary implementation elements of the BEAM program to estimate effect size and variance for future sample size calculations (treatment effect) and compare the BEAM program to SOC [28] in primary clinical outcomes including maternal depression and anxiety (treatment response).

### Trial design {8}

A two-armed, parallel-design RCT will occur where participants receive the 10-week app-based BEAM program (mental health and parenting treatment) or MoodMission (mental health treatment only). Mothers will be randomized to the BEAM or MoodMission program with a 1:1 allocation as per a computer-generated randomization schedule stratified by participant availability for weekly group telehealth sessions. Self-reported repeated measures data will be collected online via Research Electronic Data Capture (REDCap) [31] from mothers in both programs. Back-end BEAM App data will be collected via Google Analytics and Firebase. Assessments will occur at three timepoints: pre-intervention (T1), post-intervention (T2), and 6-month follow-up (T3). Amendments to the study protocol will be submitted to the Research Ethics Board (REB) at the University of Manitoba who will review and approve amendments prior to implementation. Participants will re-consent to amendments, if required. Any amendments will also be submitted as updates on ClinicalTrials.gov.

This trial is registered with ClinicalTrials.gov (NCT05398107) and will follow Standard Protocol Items: Recommendations for Intervention Trials (SPIRIT) guidelines [32, 33]. All procedures will be performed in accordance with the University of Manitoba’s REB (HE2021-0217) and the Helsinki Declaration. Participants will provide electronic informed consent prior to study enrollment.

## Methods: participants, interventions, and outcomes

### Study setting {9}

Participants will reside in Manitoba, Canada. Manitoba is in the center of Canada and has a population of 1.3 million. Recent results from a predominantly Manitoban sample of mothers with children 0–18 months old suggested significantly elevated rates of depression and/or anxiety since the onset of the COVID-19 pandemic [1].

### Participant identification and consent

Participants will be recruited using online social media advertisements (Facebook, Instagram, Twitter, Pinterest, Reddit), posters in Manitoba, Canada, and poster-sharing via Family Dynamics listserv. Informed consent will be collected electronically from all mothers on three occasions, before (a) the eligibility screener, (b) the MINI [34], and (c) beginning study participation. The consent processes will be documented using REDCap [31]. If funding is obtained for long-term follow-up, further consent will be obtained.

### Eligibility criteria {10}

Participants must (a) identify as a mother (i.e., biological, adoptive, foster, step-mother, or another type of woman-identifying primary caregiver), (b) have a child between 6 and 18 months old at recruitment, (c) be 18 years old or above, (d) reside in Manitoba, Canada, with access to a cellular network, (e) score > 9 on the Patient Health Questionnaire-9 Item (PHQ-9) [35] and/or the General Anxiety Disorder-7 Item (GAD-7) [36], (f) complete a psychodiagnostic mental health assessment (Mini International Neuropsychiatric Interview; MINI) [34] and pre-intervention survey before randomization, (g) meet criteria for a major depressive episode and/or anxiety disorder (i.e., panic disorder, agoraphobia, social anxiety disorder, or generalized anxiety disorder) as assessed by the MINI, (h) be available to attend weekly telehealth groups, and (i) be comfortable understanding, reading, and speaking English. Exclusion criteria include: (a) a suicide attempt in the past year, (b) self-harm in the past 6 months, and/or (c) clinically significant psychotic symptoms, posttraumatic stress disorder, or alcohol/substance use disorder (identified on the MINI 34) which, based on clinical judgement, would make it unlikely for the individual to attend weekly group telehealth sessions and/or make treatment gains. The BEAM and MoodMission programs are not suitable to treat these acute mental health needs and as such mothers deemed ineligible for these reasons will be provided with local mental health resources more appropriate for their needs.

### Participant timeline {13}

See Table 1 for the SPIRIT schedule of enrolment, interventions, and assessments and additional file 1 for the SPIRIT Checklist.

**Table 1 Tab1:** SPIRIT schedule of enrolment, interventions, and assessments

Study period					
	**Enrolment**	**Allocation**	**Intervention**	**Post-intervention**	**Follow-up**
**TIMEPOINT**	***Weeks 1–8***	**Week 9**	***Weeks 9–19***	***Weeks 19–21***	***Weeks 32–34***
**Informed consent**	X				
**Eligibility screener**	X				
**Psychodiagnostic Mental health Assessment**	X				
**Allocation**		X			
**INTERVENTIONS**					
***BEAM Program***			X		
***Mood Mission Program***			X		
**ASSESSMENTS**					
***Outcome survey***	X			X	X
***Weekly survey***			X		

#### Enrollment (weeks 1–8)

##### Eligibility screener

Mothers will complete an online questionnaire to determine eligibility. This questionnaire will include an author-compiled sociodemographic and suicidality/self-harm questionnaire as well as the PHQ-9 [35] and GAD-7 [36]. These questionnaires will determine whether they meet preliminary inclusion criteria.

##### Psychodiagnostic mental health assessment

If deemed eligible on the eligibility screener, mothers will be invited to complete a psychodiagnostics mental health assessment (i.e., MINI) [34] with trained research personnel via Zoom. The following modules of the MINI will be administered: major depressive episode, suicidality, panic disorder, agoraphobia, social anxiety disorder, posttraumatic stress disorder, alcohol use disorder, substance use disorder, psychotic disorders and mood disorders with psychotic features, and generalized anxiety disorder. Mothers meeting criteria for a major depressive episode and/or an anxiety disorder (i.e., panic disorder, agoraphobia, social anxiety disorder, and/or generalized anxiety disorder) will be deemed eligible once they complete the pre-intervention survey and consent to randomization. Those who do not meet inclusion criteria will be provided with a list of local mental health resources.

##### Pre-intervention questionnaires

All mothers deemed eligible to participate will be invited to complete a series of questionnaires via RedCap to assess baseline data of interest before allocation. See Table 2 for specific questionnaires.

**Table 2 Tab2:** Schedule for assessment administration

Study period					
**TIMEPOINT**	**Enrolment**	**Allocation**	**Intervention**	**Post-intervention**	**Follow-up**
	***Weeks 1–8***	**Week 9**	***Weeks 9–19***^v^	***Weeks 19–21***	***Weeks 32–34***
**Adverse Childhood Experiences**^**a**^	X				
**Ages and Stages Questionnaire: Social-Emotional, Second Edition** *(6, 12, 18, 24, 30, 36 months)*^b^	X			X	X
**Alcohol Use Disorder Identification Test**^**c**^	X			X	X
**Anxiety Persistence Scale**^a^				X	
**BEAM**^d^** App-Based Questionnaire**^a^				X	
**BEAM**^d^** Forum Questionnaire**^a^				X	
**BEAM**^d^** Perceived Social Support Questionnaire**^a^				X	
**BEAM**^d^** Zoom Telehealth Group Questionnaire**^a^				X	
**Cannabis, Tobacco, and Illicit Drug Use**^a^	X			X	X
**Cannabis Use Disorder Identification Test – Revised**^e^	X			X	X
**Couples Satisfaction Index – 4 Item**^f^	X			X	X
**Depression Persistence Scale**^a^	X				
**Depressive Symptom Index – Suicidality Subscale**^g^				X	X
**Emergency Health & Social Service Utilization**^a^	X			X	X
**Generalized Anxiety Disorder – 2 Item**^h^			X		
**Generalized Anxiety Disorder – 7 Item**^i^	X			X	X
**Infant Behavior Questionnaire – Very Short – Revised**^j^	X			X	X
**mHealth App Usability Questionnaire**^k^				X	
**Mini International Neuropsychiatric Interview**^l^	X				
**Mood Mission App-Based Questionnaire**				X	
**Parenting Scale** *(modified 10 item scale)*^m^				X	X
**Parenting Stress Index**^n^	X			X	X
**Parenting Stress Index** *(modified 4 item scale)*^a^			X		
**Patient Health Questionnaire – 2 Item**^o^			X		
**Patient Health Questionnaire – 9 Item**^p^	X			X	X
**Patient-Reported Outcomes Measurement Information System** *(Anger and Sleep Disturbance Subscales)*^q^	X			X	X
**Pediatric Quality of Life Inventory** *(1–12 or 13–24 months)*^r,s^	X			X	X
**Perceived Maternal Parenting Self-Efficacy Questionnaire**^t^	X			X	X
**Positive and Negative Affect Scale** *(modified 2-item scale)*^u^			X		
**Recent Stressful Experiences**^a^	X			X	X
**Sociodemographics**^a^	X				
**Substance Use Motives Measure** *(Coping Motive Subscales)*^v^	X			X	X

*Note*. ^a^Author-Compiled Questionnaire; ^b^Squires et al. (2015)^c^Babor et al. (2001)^d^BEAM = Building Emotional Awareness and Mental health^e^Adamson & Sellman (2003)^f^Funk & Rogge (2007) ^g^Stanley et al. (2021)^h^Kroenke et al. (2007)^I^Spitzer et al. (2006) ^j^IBQ-VS-R (Putnam et al., 2014) ^k^Zhou et al. (2019) ^l^Sheehan et al. (1998) ^m^Irvine et al. 1999 ^n^Barroso et al. (2016) ^o^Kroenke et al. (2003) ^p^Kroenke et al. (2001) ^q^PROMIS (Hanish et al., 2017; Pilkonis et al., 2011) ^r^Physical Functioning, Physical Symptoms, Emotional Functioning, Social Functioning, and Cognitive Functioning Subscales ^s^Varni et al. (1999) ^t^Barnes & Adamson-Macedo (2007) ^u^Watson et al. (1988) ^v^Biolcati & Passini (2019); ^v^Weekly questionnaires are only administered to those in the BEAM program

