#### Interventions (weeks 9–19) {11a}

The BEAM and MoodMission App-based programs will be offered via mobile device (both are functional on Android and iOS platforms). Participants will be provided with a mobile device, if required.

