#### Follow-up questionnaires (weeks 32–34)

Approximately 6 months following program completion, mothers will be sent a series of follow-up questionnaires via RedCap (see Tables 1 and 2).

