Additional questionnaires will assess maternal mental health (i.e., Patient Reported Outcomes Measurement Information System [PROMIS] Anger [PROMIS-A] [50] and Sleep Disturbance [PROMIS-SD] [51] subscales, Alcohol Use Disorder Identification Test [AUDIT] [52] Cannabis use Disorder Identification Test – Revised [CUDIT-R] [53], Substance Use Motives Measure—Coping Subscales [SUMM] [54], and Depression Severity Index—Suicidality Subscale [DSI-SS] [43]), parenting (i.e., Parenting Stress Index – Short Form [PSI-SF] [40], Perceived Maternal Parenting Self-Efficacy [PMP S-E] [55], and the Parenting Scale—Overreactivity Subscale [56], Couples Satisfaction Inventory 4-Item [CSI-4] [57]), and child outcomes (i.e., Ages and Stages Questionnaire: Social-Emotional Challenges – 2 [ASQ:SE-2] [58], Pediatric Quality of Life Inventory [PedsQL] [59], and Infant Behavior Questionnaire – Revised – Very Short Form—Effortful Control Subscale [IBQ-R-VS] [60]).

Data on sociodemographic characteristics will be collected in the pre- and/or post-intervention questionnaires including (a) maternal demographics (e.g., age, marital status, highest level of education, ethnicity, employment, depression persistence, anxiety persistence), (b) child demographics (e.g., child sex, age of child), and (c) household demographics (e.g., number of adults and children in the household, annual household income, community type).

Other variables known to impact adult mental health and child development will be collected including the Adverse Childhood Experiences (ACEs) Questionnaire, the author-compiled Recent Stressful Experiences Questionnaire (RSE; developed based on recommendations from the JPB research network on toxic stress at Harvard’s Center on the Developing Child) [61], and the author-compiled Emergency Health and Social Service Utilization Questionnaire.

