### Trial status

Recruitment began in January 2022 and finished in March 2022. The date of first enrollment was February 14th, 2022. The intervention launched in April 2022 (with estimated completion in December 2022 for the collection of all primary outcomes).

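### The PedsQL forms listed in Table 2 end at 24 months, but some children will be older than that at the T3 follow-up

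*Protocol article*

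**What the plan says.** - **Entry age.** Eligibility criteria {10}: the mother must "have a child between 6 and 18 months old at recruitment".
- **PedsQL forms.** Table 2 gives "1–12 or 13–24 months" and marks the instrument at enrolment, post-intervention and follow-up. The table note adds the subscales used but no older form. Outcomes {12} lists the PedsQL among the additional child outcomes.
- **T3 timing in the text.** "Approximately 6 months following program completion, mothers will be sent a series of follow-up questionnaires". Trial design {8} likewise labels T3 a 6-month follow-up.
- **T3 timing in the tables.** Tables 1 and 2, and the heading of the follow-up section itself, put T3 at weeks 32–34. Enrolment is weeks 1–8 and the intervention weeks 9–19.
- **Calendar.** Trial status gives first enrolment on 14 February 2022 and launch in April 2022, "with estimated completion in December 2022 for the collection of all primary outcomes".

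The article gives no rule for a child who is past 24 months when the PedsQL is due.

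**The concern.** A child who enters at 18 months and is assessed more than 6 months later is past 24 months, the upper end of the older listed form. At T3 such a child is either scored on a form outside its listed age range or has no PedsQL score. Either way the affected children are the older ones, so the loss or mismatch is related to age.

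What is at stake is the T3 child quality-of-life result, which would combine children inside and outside the listed range. If the PedsQL enters one of the averaged z-score aggregates in Statistical methods {20a}, the problem carries over; the article does not say which measures do. Blank PedsQL items could also count against the questionnaire completion criterion in Table 3 for a reason unrelated to the mothers' willingness to respond. The larger trial would inherit the schedule.

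**Working it through.** **Reproducing the stated T3 window.** One month is 365.25/12/7 = 4.348 weeks. Six months after week 19 is 19 + 6 × 4.348 = week 45.1. The tables give week 32, which is 13 weeks or 13/4.348 = 3.0 months after week 19. The stated window is therefore not reproduced. Counting 26 weeks from weeks 6–8 of enrolment would give weeks 32–34, but the text counts from program completion. Both timings are carried forward, with a two-week T3 window in each.

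**Gap from enrolment to T3.** Enrolment is weeks 1–8, midpoint 4.5. The shortest gap is (T3 opening − 8)/4.348, the midpoint gap (T3 midpoint − 4.5)/4.348, and the longest gap (T3 close − 1)/4.348.

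- Text (weeks 45.1–47.1): 37.1/4.348 = 8.53, 41.6/4.348 = 9.56 and 46.1/4.348 = 10.60 months.
- Tables (weeks 32–34): 24/4.348 = 5.52, 28.5/4.348 = 6.55 and 33/4.348 = 7.59 months.

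**Oldest child at T3** = 18 + gap: 26.5–28.6 months on the text's timing, 23.5–25.6 months on the tables' timing. This step needs no age distribution.

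**Share past the listed forms.** The article gives no age distribution, so I assume ages uniform over 6–18 months. Share = (18 − (limit − gap))/12, floored at zero. The limit is 24.0 months, or 25.0 if the form is meant to run to the 25-month birthday. The ranges run from the shortest to the longest gap; they are not confidence intervals.

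| T3 timing | Limit | Shortest gap | Midpoint | Longest gap |
|---|---|---|---|---|
| 6 months after completion | 24.0 | 21.1% | 29.7% | 38.3% |
| 6 months after completion | 25.0 | 12.7% | 21.4% | 30.0% |
| Weeks 32–34 | 24.0 | 0% | 4.6% | 13.2% |
| Weeks 32–34 | 25.0 | 0% | 0% | 4.9% |

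Against the 60 mothers targeted after attrition (30 per group), the 24-month rows are about 18 children (13–23) on the text's timing and about 3 (0–8) on the tables'. On the text's timing the affected children are those older at entry than 24 − 9.56 = 14.4 months (13.4–15.5).

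**Sensitivity to age shape.** At the text's midpoint gap and a 24.0-month limit, age distributions skewed young give about 8%, and one skewed old gives about 51%.

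**Calendar check.** From 14 February 2022 to 1–31 December 2022 is 9.5–10.5 months, or 29–38% past 24 months for a mother enrolled on the first day. For one recruited on 31 March the gap is 8.0–9.0 months, or 17–25%. These gaps are close to the text's timing, but they do not by themselves settle which passage is meant.

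**T2.** The oldest child is 18 + 11/4.348 = 20.5 to 18 + 20/4.348 = 22.6 months, so T1 and T2 lie within the listed forms.

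**The case against.** The strongest reply is that Table 2's own column puts T3 at weeks 32–34, where the problem is 0–13%, and possibly nil. The larger figure depends on the text's timing, and the conflict between the two is a separate defect. That is right, and no single percentage can be stated until the timing is reconciled. Even so, on weeks 32–34 the oldest, earliest-enrolled children reach 25.6 months.

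A second reply is that this is a condensed article and the full protocol may say what is done with a child who ages out. The forms, however, are stated in Table 2, and as stated they do not span the trial's own ages.

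A third is that the consequence is small. The PedsQL is one of many additional questionnaires, allocation is 1:1 at random so out-of-range ages should fall similarly in both arms, child age is already collected, and missing data are handled by full information maximum likelihood. Most of this stands and keeps the point minor. Maximum likelihood deals with absent scores, though, and does not correct scores taken on a form outside its listed range.

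Four stronger readings are tempting and not supported:
- That these children have no valid form. The documents show only that none is listed in Table 2. They do not say whether another form exists or how scores behave just past the limit.
- That 30% is a ceiling. It is a midpoint under an assumed age distribution and one of two timings.
- That the ASQ:SE-2 row, with forms at "6, 12, 18, 24, 30, 36 months", shows that ageing past 24 months was foreseen there and overlooked here. No child exceeds 28.6 months, so that row may simply list the instrument's forms.
- That the treatment comparison is biased. Nothing in the documents shows a difference between arms.

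**Conclusion.** The point holds as a minor one. The listed PedsQL forms do not cover all children at T3 on either stated timing. That conclusion rests only on the entry age limit, the week numbers and the listed form ages, with 24 months read as the 24-month birthday. If the form runs to the 25-month birthday, the weeks 32–34 timing leaves only the extreme case (25.6 months).

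The size is less certain. It rests on uniform entry ages, on which T3 timing is meant, and on where the older form ends. Across these readings the midpoint share runs from nil to about 30%.

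Pre- and post-intervention PedsQL scores and the PHQ-9 and GAD-7 effect and variance estimates are not affected. Nor are the feasibility indicators, apart from possible blank items in questionnaire completion.

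**What to change.** 1. Reconcile weeks 32–34 with 6 months after program completion, so that T3 has one definition in the text, the section heading and both tables.
2. In Table 2, list for T3 a PedsQL form whose age range covers children over 24 months, and carry this into the future trial.
3. T3 data may already be in: collection was due to end in December 2022 and this protocol version is dated February 2023. In that case, report T3 PedsQL for children within the listed age range at completion, deriving age from the child age already collected, and show all T3 scores as a sensitivity analysis.

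The cost is a table entry or a sentence of analysis text. The downside is fewer in-range T3 PedsQL records under the third step, or one more change of form within the longitudinal series under the second.
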